# Prohibited Concomitant Medications and Therapies

1) In principle, subjects will be prohibited from taking any of the following medications unless the principal investigator or subinvestigator allows the concomitant use in response to acute exacerbation:

ATP solution (e.g., Adetphos^Ⓡ^), Vitamin B12 solution (e.g., Methycobal^Ⓡ^), Betahistine (e.g., Merislon), and medications that improve microcirculation (e.g., Kallikrein).

2) Subjects will be prohibited from concomitant use of medications described below.

Sirolimus is metabolized by a drug-metabolizing enzyme CYP3A4, and is a substrate for P-glycoprotein. Sirolimus itself is an inhibitor of CYP3A4. Subjects are thus prohibited from taking any of the medications and foods listed below throughout their participation in this clinical trial, i.e., from the initial administration of investigational products (V1) to the end of the administration (V12).

| Influencing factors | Medications and food | Rationale |
| --- | --- | --- |
| 1) Inhibition of mTOR | everolimus; temsirolimus | The products have the same mechanism of action as the investigational products, which would disturb efficacy analysis. |
| 2) Influence on the assessment of the disease studied | aminoglycoside class of antibiotics; platinum-based drugs | Ototoxicity of the products could exacerbate inner ear disorder.  (Topical administration is allowed.) |
| 3) Live vaccines | live vaccines (e.g., measles, mumps, rubella, oral polio, BCG) | The immunosuppresive properties of sirolimus may cause proliferation of microorganisms in live vaccines leading to enhanced virulence.  (The package insert of Rapamune states these as contraindications for concomitant use.) |
| 4) Induction of CYP3A4 | anticonvulsants (e.g., carbamazepine, phenobarbital, phenytoin); rifampicin*; rifabutin; foods containing St. John’s Wort (*Hypericum perforatum*) | The products induce CYP3A4 and may lower blood concentrations of the investigational products.  (*Rifampicin induces P-glycoprotein and thus may stimulate removal of the investigational products from cells.) |
| 5) Inhibition of CYP3A4 | ciclosporin**; diltiazem**, triazole antifungal (e.g., fluconazole, ketoconazole**, itraconazole, voriconazole); HIV protease inhibitors (e.g., indinavir, ritonavir, telaprevir, saquinavir); macrolide class of antibiotics (e.g., erythromycin, clarithromycin); calcium channel blocker (e.g., nicardipine, verapamil); cimetidine; metoclopramide; bromocriptine; danazol; grapefruit juice | The products significantly inhibit CYP3A4, and may raise blood concentrations of the investigational products.  (Topical administration is allowed.)  (**These products inhibit P-glycoprotein and thus may hinder removal of the investigational products from cells.) |
| 6) Inhibition of CYP3A4 by ritonavir | ombitasvir hydrate; paritaprevir hydrate; ritonavir | Inhibition of CYP3A4 by ritonavir may raise AUC and C_max_ of the investigational products. |
| 7) Mechanism unidentified | micafungin sodium | The product may increase AUC of the investigational products. |
| 8) Other effects | angiotensin-converting-enzyme inhibitor | For a patient taking medications related to angioedema, the product may increase risks of onset of angioedema (e.g., swelling of face, lips, tongue, or throat). (Mechanism unidentified) |

# Oversight of Subjects

The principal investigator, subinvestigator, or clinical research coordinators will instruct the subjects on the following matters:

1) To undergo medical examinations and tests on designated dates. If the subject is unable to visit the institution on the date specified, the subject should contact the principal investigator, subinvestigator, or clinical research coordinator and follow their instructions.

2) To report to the principal investigator, subinvestigator, or clinical research coordinator regarding the use of all medications prescribed by doctors not involved in this trial and those purchased from pharmacists

3) Not to change their normal lifestyle, such as exercise or dietary habits, as far as possible

4) To contact the principal investigator, subinvestigator, or clinical research coordinator immediately in case any indisposition is felt

5) To adopt highly effective contraception during participation in the trial

# Tests, Observations, and Assessment

## Schedule for Tests, Observations, and Assessment

The items to be covered in tests and observations, and the schedule of the trial are shown in Table 1.

Tests and observations, and entry of the results into the electronic case report forms, can be performed by the clinical research coordinator under the oversight of the principal investigator or subinvestigator.

## Subjects’ Baseline Information

The principal investigator or subinvestigator will collect the baseline information listed below from each subject during the period between informed consent and before administration of the investigational products in V1 (D1), and record the information on the subject’s electronic case report form. For the purpose of this protocol, an illness that has not subsided before administration of the investigational products is referred to as a concomitant illness, and one that has subsided as a past medical history. The results of SLC26A4 genetic testing will not be recorded on the electronic case report form.

・Date of birth

・Gender

・Height and weight

・History of head trauma

・Concomitant illness

・Prior treatment (cisplatin and gentamicin)

・Concomitant medications

・SLC26A4 Genetic testing results

## Concomitant Medications and Therapies

The principal investigator or subinvestigator will examine concomitant medications and therapies from the screening phase (V0) to V13, and record the results on the electronic case report forms.

## Medication Adherence

The principal investigator or subinvestigator will inquire subjects about medication adherence from V1 to V12 and record the results on the respective electronic case report forms.

## Clinical Questionnaire

The principal investigator or subinvestigator will ask subjects to complete the questionnaire specified below (ePRO) every day, in principle, from the screening phase (V0) to V13, and record the results on the electronic case report forms.

・Questionnaire on daily conditions (Annex 2)

Medication adherence, hearing loss episodes, vertigo episodes, tinnitus, ear fullness, concomitant medications, handicaps caused by dizziness/vertigo (action, feeling, and daily life)

The principal investigator or subinvestigator will ask subjects to complete the Dizziness Handicap Inventory at every visit from the screening phase (V0) to V13 and at discontinuation, and record the results on the electronic case report forms.

・Dizziness Handicap Inventory: DHI-J (Annex 3)

## Tests Using Portable Testing Devices

The principal investigator or subinvestigator will provide subjects training on the portable devices and make adjustments to the devices during the screening phase (V0). Subjects will be asked to perform tests using the portable devices listed below from V0 to V13 every night, in principle. The test results will be collected at every visit from V1 to V13 and at discontinuation.

・Portable audiometer

Audiometer AA-58 (RION Co., Ltd.) (Annex 4)

For standard pure-tone audiometry (threshold of four different frequencies for left and right ears) and recording data in ePRO.

・Wireless Frenzel scope

AirMicro Frenzel Wireless Scope (Scalar Corporation) (Annex 5)

For tests such as measurement of rotational eye movement, and direction and amplitude of nystagmus, the results of which shall be transmitted to an Android terminal for storage.

The tests will be performed regularly in the evening and as appropriate when an episode occurs, as far as possible.

・JINS MEME

JINS MEME ES_R (JIN Co., Ltd.) (Annex 6)

For tests with open and closed eyes, each lasting around 30 seconds, the results of which shall be transmitted to an Android terminal for storage.

## In-clinic Testing and Observations

### Vital Signs

The principal investigator or subinvestigator will measure the vital signs listed below during the screening phase (V0), Phase I (V1 to V4), Phase II (V5 to V12), and in case of discontinuation, and record the results on the electronic case report forms.

・Blood pressure (systolic and diastolic blood pressure)

・Pulse

・Temperature

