| Thyroid ultrasound | X |  |  |  |  | X |  |  |  | X |  |  | X |  | X |
| MRI (optional)^4^ |  |  |  |  |  | X^5^ |  |  |  |  |  |  | X^5^ |  | X^5^ |
| Cytology test (optional) |  |  |  |  |  | X |  |  |  |  |  |  | X |  | X |
| Blood collection for generation of iPS cells (optional)^6^ | X |  |  |  |  |  |  |  |  |  |  |  |  |  |  |
| Blood collection for measurement of drug concentration in blood |  |  |  |  |  | X | X | X | X | X | X | X | X |  | X |
| Clinical laboratory tests (blood sampling and urinalysis)^7^ | X | X |  | X |  | X | X | X | X |  | X |  | X | X | X |
| Physical findings (height and weight) | X | X |  |  |  | X |  |  |  |  |  |  | X |  | X |
| Blood pressure, pulse, and temperature | X | X | X | X | X | X | X | X | X | X | X | X | X |  | X |

^1^ The initial administration of investigational products in Phase II for respective subjects shall not be scheduled for the same day.

^2^ The interval between V5 and V6 and between V6 and V7 should be 10 days or more.

^3^ Applies when disqualified by the eligibility judgment.

^4^ An image taken at an external institution may be used if the date of imaging falls within the allowable window and is obtained with the consent of the patient.

^5^ The allowable visit windows are to be four weeks before V5, four weeks after V12, and four weeks after discontinuation. This examination may be performed on an alternative date as an exception.

^6^ If blood was collected in the past for generation of iPS cells, and consent for its use for the clinical trial has been obtained, blood collection need not be newly performed.

^7^ Hematocrit, serum triglyceride, viral tests, thyroid autoantibody tests, pregnancy test are performed at V0 only. Thyroid hormone tests are performed at V1, V5, V12, and discontinuation only.

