# Endpoints

[Primary Endpoints]

Safety and tolerability:

1) Adverse events (nature, frequency and severity)

2) Side effects (nature, frequency and severity)

3) Clinical laboratory tests

4) Vital signs (blood pressure, pulse, and temperature)

[Secondary Endpoints]

Efficacy:

1) Frequency of hearing loss episodes (number of occurrences/year)

2) Highest measurement of auditory threshold shift at a hearing loss episode (dB)

3) Frequency of dizzy spells (number of occurrences/year)

4) Maximum amplitude (°/sec) and maximum frequency (cycle/sec) of nystagmus during a hearing loss episode

5) Percentage of cases in which increase in hearing threshold was observed during remission in the observation period (comparison of measurements at the end of Phase I and the end of Phase II)

6) Improvement in hearing threshold during remission

7) Shorter duration of hearing loss episodes

8) Alleviation of symptoms of dizziness/vertigo

Changes in total scores of the Dizziness Handicap Inventory from Phase I to Phase II

9) Percentage of cases in which equilibrium exacerbated during remission in the observation period (comparison of measurements at the end of Phase I and the end of Phase II)

[Exploratory Endpoints]

1) Reduction in endolymphatic hydrops (MRI findings)

2) Inhibition of goiter or thyroid enlargement

3) Cell biological changes in thyrocytes detected by cytology tests

4) Comparison of results of in vitro efficacy evaluation of inner ear cells derived from PDS-specific iPS cells and of clinical evaluation

5) Deviation from threshold value for frequency of abnormalities of auditory brain stem responses and for pure-tone audiometry

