### Laboratory Tests

The principal investigator or subinvestigator will perform the following laboratory tests during the screening phase (V0), Phase I (V1 and V3), Phase II (V5, V6, V7, V8, and V12), follow-up observations (V13), and at discontinuation, and record the results on the electronic case report forms.

[Laboratory test items]

| Tests | Variables |
| --- | --- |
| Hematological tests | red blood cell count, hemoglobin, reticulocyte count, white blood cell count, platelet count, lymphocyte count, neutrophil count, and hematocrit (V0 only) |
| Blood biochemical tests | creatinine, ALP (Changes in the level of ALP will be analyzed as a blood marker), total bilirubin, AST, LDH, ALT, BUN, albumin, CRP, total cholesterol, LDL-cholesterol, uric acid, Na, K, Ca, P, Cl, fasting blood glucose, and serum triglyceride (V0 only) |
| Thyroid hormone tests | FT3, FT4, and TSH (all of these are performed at V1, V5, V12, and discontinuation only) |
| Urinalysis | pH, sugar, protein, and occult blood in urine |
| Viral test | HBs antigen, HBs antibody, HBc antibody, HCV antibody, and HIV antibody (all of these will be performed at V0 only) |
| Thyroid autoantibody tests | TgAb, TPOAb, and TRAb (all of these will be performed at V0 only) |
| Pregnancy test | hCG urine (V0 only) |

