## Adverse Events

### Definition of Adverse Events

An adverse event in this trial refers to any untoward medical occurrence in a subject from initial administration of investigational products (V1) to follow-up observations (V13). The event may not necessarily have to have a causal relationship with administration of investigational products in this trial. An adverse event can therefore be any unfavorable and unintended sign (including an abnormal laboratory finding, for example), symptom, or disease temporally associated with the use of a medicinal product, whether considered related to the medicinal product or not.

Exacerbation of the primary disease, including episodes, will not be regarded as an adverse event, with the exception of cases in which causal relationship with the investigational products cannot be ruled out.

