### Assessment of Adverse Events

The items listed below will be examined and recorded on the electronic case report forms with regard to adverse events that occur from the initial administration of investigational products (V1) to follow-up observations (V13).

If a diagnosis is settled based on signs or symptoms, the diagnosis rather than the signs or symptoms should be recorded. With regard to vital signs and clinical test measurements, changes from conditions before administration of investigational products should be assessed to determine whether the changes are clinically significant. An abnormal change that is considered clinically significant is to be counted as an adverse event. An abnormal change that is relevant to symptoms and signs already recognized as an adverse event, shall not be required to be newly reported as a separate adverse event.

・Name of the adverse event

・Date of occurrence

・Severity

・Seriousness

・Actions taken (administration of investigational products or other actions)

・Outcome and date of outcome confirmation

・Causal relationship with the investigational products

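### Vital signs, a primary safety endpoint, are not scheduled at the V13 follow-up visit, so completers have no routine reading after dosing ends

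*Protocol*

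**What the plan says.** - **Status of the endpoint.** The Protocol's Endpoints section lists, among the primary safety and tolerability endpoints, "4) Vital signs (blood pressure, pulse, and temperature").
- **When they are measured.** Besides screening, 14.7.1 gives "Phase I (V1 to V4), Phase II (V5 to V12), and in case of discontinuation". V13 is not named. In Table 1 the row that opens "Blood pressure, pulse, and temperature | X | X" is blank under V13 and marked under Discontinuation. The synopsis table is the same.
- **When dosing ends.** The section on prohibited concomitant medications describes the dosing period as running "from the initial administration of investigational products (V1) to the end of the administration (V12").
- **What happens at V13.** It is an in-clinic visit at week 40. Laboratory tests are scheduled there, since the list in 14.7.3 closes with "follow-up observations (V13), and at discontinuation". Audiometry and posturography are also done.
- **Adverse events.** The window in 14.10.1 runs "from initial administration of investigational products (V1) to follow-up observations (V13"). Section 14.10.2 adds: "With regard to vital signs and clinical test measurements, changes from conditions before administration of investigational products should be assessed". It counts clinically significant abnormal changes as adverse events.
- **Follow-up.** Section 14.10.7 has recognised adverse events followed, in principle, until they resolve or return to the prior state.
- **Analysis.** Section 17.4.2 summarises clinical tests and vital signs by arm and does not name the visits.

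**The concern.** Section 14.10.2 treats vital signs and clinical tests as parallel sources for detecting adverse events, within one window that ends at V13. The schedule supplies a V13 measurement for the main laboratory panels but not for vital signs. Both are primary safety endpoints and the visit is the same one, yet the protocol gives no reason for the difference.

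At stake is the off-treatment description of one primary safety endpoint. With four placebo subjects, a between-arm comparison of blood pressure or pulse is weak, so change within a subject on and off drug carries more of the weight. The schedule gives readings before and during active treatment but none afterwards for those who complete it. An unseen SAP cannot repair this, because it cannot analyse a measurement that was not taken.

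**Working it through.** **1. Confirm that dosing ends at V12.** The visit table puts V5 at week 12 (±3 days) and V12 at week 36 (±7 days). The protocol states maximum dosing periods of 178 days (active) and 259 days (placebo).
- Active: (36 − 12) × 7 + 3 + 7 = 168 + 10 = 178 days.
- Placebo: 36 × 7 + 7 = 252 + 7 = 259 days.

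Both stated figures are reproduced exactly with V12 as the end of dosing.

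**2. Read the schedule rows across the 15 columns (V0 to V13 plus Discontinuation).**

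| Item | Visits up to V12 | V13 | Discontinuation |
|---|---|---|---|
| Blood pressure, pulse, temperature | V0 to V12 (13 visits) | none | yes |
| Laboratory tests | V0, V1, V3, V5, V6, V7, V8, V10, V12 | yes | yes |

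The vital-sign row is the same in both tables and matches 14.7.1, so the blank cell is not an extraction fault. For the laboratory tests, 14.7.3 does not list V10, but it agrees with the tables on V13.

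**3. Check which laboratory items reach V13.** Thyroid hormones are measured only at V1, V5, V12 and discontinuation. Hematocrit, triglyceride, viral, autoantibody and pregnancy tests are V0 only. The rest of haematology and biochemistry, and urinalysis, continue to V13. The comparison holds for the core panels, not for every item.

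**4. Length of the interval without a scheduled reading.** V12 is at week 36 and V13 at week 40, each ±7 days.
- Nominal: (40 − 36) × 7 = 28 days.
- Shortest: 28 − 7 − 7 = 14 days.
- Longest: 28 + 7 + 7 = 42 days.

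**5. Count readings for an active-arm completer,** taking the V5 reading as made before the first Phase II dose.
- Before active drug: V0 to V5, 6 readings.
- On active drug: V6 to V12, 7 readings.
- After active drug: 0 as written, 1 if V13 is added.

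**6. Separate what is covered from what is not.**
- *Covered:* a clinically significant change found by V12. It is an adverse event under 14.10.2 and is followed to recovery under 14.10.7, beyond V13 if need be.
- *Covered:* a change with symptoms after V12, reported by the subject or noted at V13.
- *Not measured:* a new change without symptoms that first appears after V12.
- *Not measured:* the return to pre-treatment level of shifts judged not clinically significant, or visible only in the arm-level summaries of 17.4.2.

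**7. Number of subjects.** All completers, up to 16, lack the reading. The question of reversal concerns at most the 12 on active drug, because the 4 on placebo have no drug effect to reverse.

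**The case against.** The strongest reply is that the protocol already protects what matters.

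- **Follow-up of adverse events.** Section 14.10.7 obliges the investigator to follow any adverse event to recovery, so a clinically significant vital-sign change at V12 would be rechecked. This stands, and it removes the most serious part of the concern.
- **The adverse-event rule still works.** A reader might infer that the vital-sign part of 14.10.2 cannot operate after V12, or that late change cannot be seen. The protocol does not support that. The rule says how a reading is judged and does not demand a scheduled reading throughout the window. Subjects are told to report any indisposition at once and they attend the clinic at V13. Only the routine reading is missing.
- **No contradiction.** A reader might also infer that the sections conflict. They do not: 14.7.1 and both tables agree. An adverse-event window that outlasts some scheduled assessments is not an error in itself, and height and weight also stop at V12.
- **Other own-control information.** There is a 12-week placebo run-in with readings, dosing can be suspended for adverse events, and withdrawn subjects have a discontinuation reading. One unreplicated reading 14 to 42 days after V12 is weak evidence of reversal. This is fair and limits the value of the addition.

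None of these points provides a routine post-treatment reading for a completer, or explains why the core laboratory panels get one and vital signs do not.

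**Conclusion.** The point holds as a minor, consistent design gap. Completers have no scheduled vital signs over about 28 days after dosing ends (14 to 42 by the visit windows), although they attend the clinic at V13 for other safety tests. This leaves unmeasured any new symptom-free change after V12, and any reversal of sub-threshold or group-level shifts in up to 12 active-arm subjects.

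The interval is 4 of the 40 weeks from V1 to V13, or 10% of calendar time. A reader might take that as 10% of the safety information, but what is absent is one visit's readings after 13 scheduled ones. No planned test, significance level or sample size depends on it.

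The conclusion assumes that dosing stops at or close to V12, as the reproduced maximum periods indicate, and that no separate procedure has vital signs recorded at V13.

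**What to change.** Add blood pressure, pulse and temperature at V13 in 14.7.1 and in the vital-sign row of both schedule tables (synopsis and Table 1). State in 17.4.2 that the vital-sign summaries include V13. If the omission is deliberate, give the reason instead.

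The cost is a few minutes per subject at a visit that already takes place, one eCRF field set and an amendment line. No extra visit or staff is needed.

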### Physical Findings

The principal investigator or subinvestigator will measure the physical findings listed below during the screening phase (V0), Phase I (V1), Phase II (V5 and V12) and in case of discontinuation, and record the results on the electronic case report forms.

・Height

・Weight

### Laboratory Tests

The principal investigator or subinvestigator will perform the following laboratory tests during the screening phase (V0), Phase I (V1 and V3), Phase II (V5, V6, V7, V8, and V12), follow-up observations (V13), and at discontinuation, and record the results on the electronic case report forms.

[Laboratory test items]

| Tests | Variables |
| --- | --- |
| Hematological tests | red blood cell count, hemoglobin, reticulocyte count, white blood cell count, platelet count, lymphocyte count, neutrophil count, and hematocrit (V0 only) |
| Blood biochemical tests | creatinine, ALP (Changes in the level of ALP will be analyzed as a blood marker), total bilirubin, AST, LDH, ALT, BUN, albumin, CRP, total cholesterol, LDL-cholesterol, uric acid, Na, K, Ca, P, Cl, fasting blood glucose, and serum triglyceride (V0 only) |
| Thyroid hormone tests | FT3, FT4, and TSH (all of these are performed at V1, V5, V12, and discontinuation only) |
| Urinalysis | pH, sugar, protein, and occult blood in urine |
| Viral test | HBs antigen, HBs antibody, HBc antibody, HCV antibody, and HIV antibody (all of these will be performed at V0 only) |
| Thyroid autoantibody tests | TgAb, TPOAb, and TRAb (all of these will be performed at V0 only) |
| Pregnancy test | hCG urine (V0 only) |

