# Administration of Investigational Products

Figure 1 Dosing Protocol

Phase I (single-blind): NPC-12T placebo tablets for 3 months (12 weeks)

Phase II (double-blind): NPC-12T active substance tablets or NPC-12T placebo tablets for 6 months (24 weeks)

[Dosage at the outset of the trial]

Subjects weighing less than 40 kg will take one 1-mg tablet orally once every other day.

Subjects weighing 40 kg or more will take one 1-mg tablet orally once per day.

The investigational products are to be taken before sleep.

The bodyweight measured at V1 will be referred to in determining dosage throughout the trial.

<Rationale for the dosing time>

The package insert of Rapamune 1 mg tablets was referred to when setting the dosing time. The insert cites reports that state administration of the tablet after a high-fat meal increased the blood concentration of sirolimus. To reduce effects of high-fat meals, the dosing time of the investigational products is set to be before sleep.

[Prescription of the investigational products]

In Phase I (V1, V2, V3, and V4) and Phase II (V5 and V6), the principal investigator or subinvestigator will prescribe investigational products in accordance with the dosage at the start of the trial described above.

In Phase II (V7, V8, V9, V10, and V11), the unblinded doctor will instruct the principal investigator and subinvestigators on the prescription of the investigational product based on the criteria for dosage change. The principal investigator or subinvestigator will make a judgment on whether dosage reduction is required or dosage increase is permissible, taking account of subjects’ safety, including risks of adverse events. If the conditions are deemed appropriate, the principal investigator or subinvestigator will prescribe the investigational products as instructed by the unblinded doctor. The unblinded doctor will provide instructions to the principal investigator or subinvestigator in accordance with the trough concentration measurements and the prescription schedule generated by the randomization manager. The trough concentration measurements and the prescription schedule are not to be disclosed to any person except the unblinded CRCs until the end of the trial, and will be kept securely locked in a cabinet accessible only to the unblinded doctor.

[Criteria for dosage change]

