If the prescription schedule specifies reduction, the unblinded doctor will instruct the principal investigator or subinvestigator regarding dosage reduction for NPC-12T placebo. The dosage level will be lowered by one tier at a time. The reduced dosage must be no lower than one 1-mg tablet every three days, administered orally. If further reduction is required, administration of the investigational products will be discontinued.

If the principal investigator or subinvestigator determines further reduction is required, administration of the investigational products will be discontinued.

The unblinded doctor will provide instructions to the principal investigator or subinvestigator on prescription in accordance with the specified dosage change in the prescription schedule. The decision by the principal investigator or subinvestigator on permission for dosage increase and reduction shall take precedence over the specification in the prescription schedule, i.e., if the principal investigator or subinvestigator specifies reduction, and the prescription schedule states increase, reduction should be adopted.

[Acceptable change in dosage]

The amounts of investigational products to be administered can be increased or decreased to one of the following dosages:

A. Two 1-mg tablets, once per day, administered orally

B. One 1-mg tablet, once per day, administered orally

C. One 1-mg tablet, once every other day, administered orally

D. One 1-mg tablet, once every three days, administered orally

[Dosage reduction or increase]

When dosage is to be increased, the dosage level should be raised by one tier at a time: Subjects weighing 40 kg or over will follow the change from B to A. Subjects weighing below 40 kg will follow the change from C to B to A.

When dosage is to be reduced, the dosage level should be lowered by one tier at a time, from A to B to C to D. If the current level for a subject is B, for example, C will be applied in the next reduction. If further reduction below D is required, administration of the investigational products to the subject will be discontinued.

[Suspension or reduction of administration of investigational products due to adverse events]

・Unacceptable adverse events or exacerbation considering the safety of the subject

・Unacceptable abnormal observations in clinical tests considering the safety of the subject

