### Caloric Test

The principal investigator or subinvestigator will perform a caloric test during the screening phase (V0), Phase II (V5, V9, and V12), and at discontinuation, and record the results on the electronic case report forms.

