## Blood Concentration of Sirolimus

The principal investigator or subinvestigator will collect blood for analysis of blood concentration of sirolimus during Phase II (V5, V6, V7, V8, V9, V10, V11, and V12). Analysis of the blood will be entrusted to an external contractor.

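### Section 14.7.3 omits the V10 laboratory tests that Table 1 and the synopsis schedule both require; followed as written, it leaves no scheduled safety laboratory test between weeks 20 and 36

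*Protocol*

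**What the plan says.** Section 14.7.3 tells the investigator to run the laboratory panel at V0, V1 and V3, in "Phase II (V5, V6, V7, V8, and V12"), at V13 and at discontinuation. V10 is not in the list.

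Table 1 has a row headed "Clinical laboratory tests (blood sampling and urinalysis"), marked at V0, V1, V3, V5, V6, V7, V8, V10, V12, V13 and discontinuation. The synopsis schedule carries the same row with the same marks. Footnote 7, attached to that row, restricts only certain items: some are done at V0 only, and thyroid hormones at V1, V5, V12 and discontinuation only. It does not exempt haematology, biochemistry or urinalysis at V10.

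Section 14.1 says that the items and "the schedule of the trial are shown in Table 1".

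Two other provisions bear on the point. The Endpoints section makes clinical laboratory tests the third primary endpoint. Under Administration of Investigational Products, one of the two grounds for suspending and then reducing the dose is "Unacceptable abnormal observations in clinical tests considering the safety of the subject". The same section places the instructed dose changes in the later treatment visits: "In Phase II (V7, V8, V9, V10, and V11), the unblinded doctor will instruct".

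**The concern.** The protocol gives two different laboratory schedules for the treatment period, and the shorter one is in the section that tells the investigator what to do. V10 is the only laboratory visit on which they differ, but it sits in the middle of the longest stretch. Without it, nothing is scheduled after V8 (week 20) and before V12 (week 36), which is 16 of the 24 weeks of Phase II.

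Doses may still be raised in that stretch. The dose-suspension rule for unacceptable test findings would have no scheduled laboratory input there. Laboratory abnormalities that count as adverse events under Section 14.10.2 could also be found later than intended. Subjects may be as young as seven.

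There is also a compliance problem. Sections 16.1 and 16.2 require investigators to follow the protocol and record every deviation. As written, testing at V10 departs from Section 14.7.3, and not testing departs from Table 1.

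**Working it through.** **Is the V10 mark real?** Each schedule has 15 visit columns (V0 to V13 plus discontinuation), and the laboratory row has 15 cells in both. Matching cells to headers puts marks at weeks -2, D1, 4, 12, 14, 16, 20, 28, 36 and 40, and at discontinuation. As a control, the pure-tone audiometry row read the same way gives V0, V1, V3, V4, V5, V7 to V13 and discontinuation, which is exactly the list in Section 14.7.5. The V10 mark is therefore not an artefact of table layout.

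**Inputs.** Visit weeks from Table 1: V7 = 16, V8 = 20, V9 = 24, V10 = 28, V11 = 32, V12 = 36. The window is ±7 days at V8, V10 and V12. Windows are taken around the nominal visit day.

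**Gap under the text (V8 to V12).**
- Nominal: 7 × (36 − 20) = 112 days.
- Longest within windows: 112 + 7 + 7 = 126 days. Shortest: 112 − 7 − 7 = 98 days.

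**Gaps under the tables (V8 to V10, and V10 to V12).**
- Nominal: 7 × (28 − 20) = 56 days and 7 × (36 − 28) = 56 days.
- Longest within windows: 56 + 7 + 7 = 70 days for either one.

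**On-treatment laboratory time points**, taking V5 as pre-dose:
- Text: V6, V7, V8, V12 = 4.
- Tables: V6, V7, V8, V10, V12 = 5.

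**Weeks from a dose change to the next scheduled laboratory test:**

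| Dose change at | Text | Tables |
|---|---|---|
| V7 (week 16) | 20 − 16 = 4 | 20 − 16 = 4 |
| V8 (week 20) | 36 − 20 = 16 | 28 − 20 = 8 |
| V9 (week 24) | 36 − 24 = 12 | 28 − 24 = 4 |
| V10 (week 28) | 36 − 28 = 8 | 36 − 28 = 8 |
| V11 (week 32) | 36 − 32 = 4 | 36 − 32 = 4 |

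Only changes at V8 and V9 are affected. The permitted dose steps show what this could mean. A subject under 40 kg starts at 1 mg every other day (0.5 mg/day on average) and may rise by two tiers to 2 mg/day, a factor of 2 / 0.5 = 4. If those two steps fell at V8 and V9, the text would schedule the next laboratory test at week 36 and the tables at week 28.

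**Which source is right?** Both tables include V10, and Section 14.1 points to Table 1, so the text is the likely error. Table 1 is not free of errors, however. Section 14.7.8 says to "perform a caloric test during the screening phase (V0), Phase II (V5, V9, and V12"); Section 14.7.9 gives the same visits for c-VEMP, and the synopsis agrees, yet Table 1 has no mark for these tests at V9. Conversely, Table 1 marks thyroid ultrasound at V9, which neither Section 14.9.2 nor the synopsis does.

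**The case against.** The strongest reply is that the protocol already resolves the conflict. Section 14.1 refers to Table 1, the synopsis agrees with it, and the 16-week gap arises only if a site reads one sentence and disregards both schedules. On this view the point is an editorial slip, not a deficient monitoring design.

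Much of this stands. The harm is conditional, and nothing suggests that a 16-week interval was chosen. Other monitoring also continues: vital signs are taken throughout "Phase II (V5 to V12), and in case of discontinuation", sirolimus troughs are sampled "during Phase II (V5, V6, V7, V8, V9, V10, V11, and V12"), and a trough above 7.5 ng/mL still prompts a reduction. Doses move one tier at a time to a ceiling of 2 mg/day, adverse events are assessed continuously, and subjects are told to report any indisposition at once. The suspension rule does not require that a test be a scheduled one. Sample size and inference are unaffected; the analysis cost is one descriptive time point.

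Two parts do not hold. The reference to Table 1 is a weak tiebreaker, because Table 1 is wrong at V9 for caloric/c-VEMP and thyroid ultrasound, and a site that notices this could reasonably trust the section text instead. And the continuing monitoring does not substitute for the panel. Trough values are withheld from the blinded investigators, and neither troughs nor vital signs supply haematology, biochemistry or urinalysis.

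**Conclusion.** The concern holds. Section 14.7.3 contradicts Table 1 and the synopsis at one visit, V10, and the text is very probably the side in error. If the text is followed, the longest scheduled laboratory gap doubles from 8 to 16 weeks, one of five on-treatment time points for a primary endpoint is lost, and the wait after a dose change at V8 or V9 lengthens by 8 weeks. If the tables are followed, nothing is lost. The figures assume nominal visit weeks with the stated windows, V5 as pre-dose, and no unscheduled testing. This is an internal inconsistency that should be corrected because it affects the safety schedule; it does not undermine the trial's analysis.

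**What to change.** In Section 14.7.3, change the Phase II list to V5, V6, V7, V8, V10 and V12. This restores 8-week intervals from week 20 to week 36. It adds no visit and no extra venepuncture occasion, since V10 already takes place with blood drawn for drug concentration; the panel itself is already budgeted for in both tables.

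Separately, correct Table 1 at V9: add the caloric and c-VEMP mark and remove the thyroid ultrasound mark, so that it matches the synopsis and Sections 14.7.8, 14.7.9 and 14.9.2. While the schedule is open, reconcile three smaller mismatches between the tables and the text: speech audiometry at V13, auditory brainstem response at discontinuation, and drug concentration at discontinuation, each marked in the tables but not listed in its section. All of these are wording changes in a single amendment.
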